AL-335 is metabolized by esterases. It has demonstrated a low inhibition potential to CYP1A2, CYP2B6, CYP2C8, CYP2C9, CYP2C19, CYP2D6 and CYP3A4 ( $IC_{50} > 26 \mu M$ ). The metabolites, ALS-022399 and ALS-022227, did not show any inhibition to CYP2B6, CYP2C8 and CYP3A4, CYP450s that have been tested to date. AL-335 and metabolites are not expected to cause drug–drug interaction with other drugs that are metabolized by cytochrome P450 enzymes. However, as a precaution, subjects should not receive any medications known to be an inducer or inhibitor of liver enzymes within 3 weeks prior to receiving study medication until completing the study unless they receive treatment for CHC.

AL-335 was well tolerated in all toxicology studies. Following 14 days of repeated oral dosing, the target organs for toxicity were not identified even when dosed up to the maximum recommended doses of 1000 mg/kg/day in both rats and dogs. No significant changes in the hematology, serum chemistry or histopathological changes in either species when dosed for 14-day up to 1000 mg/kg/day, the highest dose tested. Other non-adverse, minimal, non-physiologically relevant changes reported include slight increase in heart rate (~10%) and body temperature (< 1°C) in the dog cardiovascular study following single dose of 1000 mg/kg dose. The 1000 mg/kg/day was considered the no-observed-adverse-effect-level (NOAEL) in both rats and dogs, where highest steady state  $AUC_{0-24}$  for AL-335, ALS-022399 and ALS-022227 were 2490, 22900 and 75500 ng·h/mL, respectively.

Infrequent but serious adverse events associated with mitochondrial toxicity, such as myopathy, lactic acidosis, hepatomegaly with steatosis, neuropathy, and pancreatitis, have been observed with chronic administration of nucleos(t)ide analogs for the treatment of HIV infection ([Lewis and Dalakas 1995](#)) and chronic hepatitis B ([Fontana 2009](#)). The risk of developing any of these abnormalities in the phase 1 program is considered to be very low as AL-335 did not exhibit mitochondrial toxicity in vitro and the durations of dosing in the phase 1 studies is short.

As of 10 April 2015, forty (40) healthy volunteers have received single doses up to 1200 mg (SAD) or two 400 mg doses (Part 2) of study medication. There were no SAEs, and no clinically relevant laboratory, ECG, Holter, vital sign, or physical exam safety signals have

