All 8 healthy volunteers or 8 of the 10 subjects with CHC in each cohort must complete the dosing schedule before a decision is made to proceed to subsequent dosing cohorts. Additional subjects may be recruited to evaluate a dose further if the data obtained from the initial cohort is not sufficiently robust for any given dose level. A decision to replace subjects for reasons other than safety-related will be made by the Sponsor in consultation with the PI.

Dose escalation will be suspended:

- If 4 or more subjects in a dose cohort experience moderate AEs or toxicities considered possibly or probably related to study drug, OR
- If 2 or more subjects in a dose cohort experience severe AEs or toxicities considered possibly or probably related to study drug, OR

- If one or more subjects in a dose cohort experience life threatening AEs or toxicities considered possibly or probably related to study drug. In this case, the Sponsor's Medical Monitor will review the treatment allocation to determine if the subject is receiving study medication or placebo. If the subject was receiving placebo then dose escalation may recommence, OR
- If 3 or more subjects in a dose cohort experience a sustained QTcF greater than 500 msec associated with an increase greater than 60 msec , OR
- If 3 or more subjects in a dose cohort experience a sustained resting heart rate of greater than 100 beats per minute

If dose escalation is suspended, a more comprehensive review of the safety data will be undertaken by the Sponsor and the PI. Based on this review, a decision will be made to continue with dose escalation, repeat a previously evaluated dose, evaluate a lower dose, modify the protocol, or terminate the study.

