#### **7.1.2      Adverse Events**

An AE is any event, side effect, or untoward medical occurrence in a subject enrolled in a clinical trial whether or not it is considered to have a causal relationship to the study drug. An AE can therefore be any unfavorable and unintended sign, symptom, laboratory finding outside of normal range with associated clinical symptoms or suspected latent clinical symptoms in the opinion of the investigator, physical examination finding, or disease temporally associated with the use of the study drug, whether or not the event is considered related to the study drug.

Planned hospital admissions or surgical procedures for an illness or disease that existed before the subject was enrolled in the study are not to be considered AEs unless the condition deteriorated in an unexpected manner during the study (e.g., surgery was performed earlier than planned).

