### **7.2.2 Documenting and Reporting Adverse Events**

**Record all AEs** that occur from Day 1 (from start of study medication administration) to the follow-up visit, regardless of the intensity, seriousness, or relationship to study drug, on the AE CRF, for all enrolled subject. Subjects who do not enroll (i.e., screen failures), collect AEs until the time of screen failure.

Grade AEs (serious and nonserious) in accordance with the scale presented below:

- Mild adverse event (minor; no specific medical intervention; asymptomatic laboratory findings only;; marginal clinical relevance); does not interfere with regular activities

- Moderate adverse event (minimal intervention; local intervention; noninvasive intervention [packing, cautery]); moderate level of discomfort and significantly interferes with regular activities
- Severe and undesirable adverse event (significant symptoms requiring hospitalization or invasive intervention; transfusion; elective interventional radiological procedure; therapeutic endoscopy or operation); significant level of discomfort and prevents regular activities
- Life-threatening or disabling adverse event (complicated by acute, life-threatening metabolic or cardiovascular complications such as circulatory failure, hemorrhage, sepsis. Life-threatening physiologic consequences; need for intensive care or emergent invasive procedure; emergent interventional radiological procedure, therapeutic endoscopy or operation).

Once an event has resolved, any recurrence will be reported as a new event with a corresponding grade.

Whenever possible, report AEs as a specific diagnosis or syndrome (e.g., flu syndrome) rather than as individual signs or symptoms. If no specific diagnosis or syndrome is identified, AEs should be reported as separate and individual events.

An AE includes the following:

- Pre-existing event that increases in frequency or intensity.
- Condition detected or diagnosed during the study period, even though it may have been present, in retrospect, prior to the first dose of study drug.
- Laboratory abnormalities outside of normal limits and requiring therapeutic intervention.
- An overdose of the study drug without any signs or symptoms will be considered an AE. A calculated dose that exceeds its correct dose by 10% or more and is administered to the subject will be considered an overdose and documented as an AE.

The following events **will not** be identified as AEs in this study:

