- Progression or exacerbation of the subject's underlying disease. However, clinical sequelae that result from disease progression, such as pleural effusion or small bowel obstruction, are reportable as AEs.
- Medical or surgical procedures (e.g., surgery, endoscopy, tooth extraction, etc); however, the condition (the "triggering event") that leads to the procedure may be an AE.
- Pre-existing conditions present or detected prior to the first dose of study drug that do not worsen.

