**Possibly Related:**

There is an association between the event and the administration of the investigational study drug and there is a plausible mechanism for the event to be related to investigational study drug, but there may also be alternative etiology, such as characteristics of the subject's clinical status or underlying disease.

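### Section 7.2.2 both includes and excludes worsening hepatitis C as an adverse event, so in Part 3 hepatic worsening short of clinical sequelae or an SAE may go unrecorded and unattributed

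*Protocol*

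**What the plan says.** **What counts as an AE.** Section 7.2.2 includes a "Pre-existing event that increases in frequency or intensity". Its list of events that are not AEs opens with "Progression or exacerbation of the subject's underlying disease". The next sentence limits that exclusion: "However, clinical sequelae that result from disease progression, such as pleural effusion or small bowel obstruction, are reportable as AEs". A later bullet in the same list excludes pre-existing conditions only where they do not worsen. No order of precedence is given.

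**Laboratory findings.** Section 7.1.2 admits a "laboratory finding outside of normal range with associated clinical symptoms or suspected latent clinical symptoms in the opinion of the investigator". Section 7.2.2 includes "Laboratory abnormalities outside of normal limits and requiring therapeutic intervention". The mild grade in Section 7.2.2 nevertheless covers purely laboratory findings without symptoms.

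**Causality.** Section 7.2.3 gives guidance for AEs and SAEs. Its possibly-related category already allows that "there may also be alternative etiology, such as characteristics of the subject's clinical status or underlying disease".

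**Where the records are used.** Section 9.2.1 says the primary endpoint may be characterised by the number of participants with adverse events of each type. Section 5.1.1 suspends escalation on counts within a cohort, for example "If 2 or more subjects in a dose cohort experience severe AEs or toxicities considered possibly or probably related to study drug". The corresponding count for moderate events is four or more subjects.

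**The concern.** Safety is the primary objective. In Part 3 the underlying disease is a liver disease, and a cohort with compensated cirrhosis may be enrolled. Section 1.1 notes that serious events including "lactic acidosis, hepatomegaly with steatosis, neuropathy, and pancreatitis, have been observed with chronic administration of nucleos(t)ide analogs", although that experience comes from long-term dosing and the section rates the risk in this programme as very low.

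Under the exclusion, the investigator decides between disease and drug before anything is written on the AE form. Two sites could see the same on-study rise in liver tests, and one could file an AE with a causality judgement while the other files nothing. An attribution that was never made at the time cannot be rebuilt at analysis. This is therefore a matter for the protocol and CRF guidelines, not one that an analysis plan can settle.

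**Working it through.** The protocol states no figure on this point, so the check is mainly a comparison of the rules.

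**1. One case under each rule.** Take a Part 3 subject whose ALT rises on study to 8 x ULN, without symptoms and without treatment. This is a hypothetical value. Exclusion criterion 21 allows entry ALT up to 5 x ULN.

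| Rule | Result |
|---|---|
| 7.2.2, worsening of a pre-existing event | AE |
| 7.2.2, underlying-disease exclusion | Not an AE if judged an exacerbation of hepatitis C |
| 7.2.2, sequelae sentence | Does not clearly apply: an ALT value is not a clinical sequela, and the examples are not hepatic |
| 7.1.2, laboratory wording | AE only with symptoms or suspected latent symptoms |
| 7.2.2, laboratory wording | Not on this line, as no treatment was needed |
| 7.2.2, severity scale | If an AE, mild |
| 7.2 and Appendix E (DAIDS) | If an AE, Grade 3, severe (above 5.0 and up to 10.0 x ULN) |

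The same finding can be no AE, a mild AE or a severe AE. Reading the exclusion as a specific exception to the general rule removes the contradiction, but it confirms that the event goes unrecorded.

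**2. Reach.** Seven to eight cohorts of 10 give 70 to 80 subjects. At 8 per cohort on AL-335, that is 7 x 8 = 56 to 8 x 8 = 64. This is a headcount, not an effect.

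**3. How sensitive a count of this kind is.** The rates below are assumptions and are not in the protocol. Let hepatic worsening of the relevant severity, judged related, be the only qualifying event, with per-subject probability p. Let f be the share recorded, and suppose unrecorded events are not picked up as toxicities or SAEs. With q = p x f, n = 10 and trigger r:

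P(trigger) = sum over k = r to n of C(n,k) q^k (1 - q)^(n - k)

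For r = 2 and q = 0.20: 1 - 0.8^10 - 10 x 0.2 x 0.8^9 = 1 - 0.1074 - 0.2684 = 0.624. For q = 0.10: 1 - 0.3487 - 0.3874 = 0.264.

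| p | Severe (2 or more), all recorded | Severe, half recorded | Moderate (4 or more), all recorded | Moderate, half recorded |
|---|---|---|---|---|
| 0.10 | 0.264 | 0.086 | 0.013 | 0.001 |
| 0.20 | 0.624 | 0.264 | 0.121 | 0.013 |
| 0.30 | 0.851 | 0.456 | 0.350 | 0.050 |

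Counting only the 8 active subjects, the severe trigger at p = 0.20 goes from 0.497 to 0.187. If nothing is recorded, every entry is 0.

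**4. What limits the table.** On the Section 7.2.2 scale, severe means hospitalisation, invasive intervention or similar, and much of that would be an SAE anyway. An asymptomatic laboratory change is only mild on that scale and enters neither count. For such changes, the effect on suspension therefore depends on reading severity from Appendix E. Section 5.1.1 names no scale.

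**The case against.** A reader might infer that hepatic worsening disappears from the primary endpoint and can never trigger a suspension. The protocol does not support that, for five reasons.

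- Section 3.2.1 names clinical laboratory results as part of the primary endpoint. Liver function tests are drawn at every Part 3 visit (Table 6.1-3), and Section 10.4.2 tabulates Grade 3 and 4 laboratory abnormalities by cohort and treatment.
- Section 5.1.1 counts toxicities as well as AEs. Appendix E is headed as toxicity tables and grades ALT, AST and bilirubin.
- Clinical sequelae of progression stay reportable. The non-hepatic examples illustrate that sentence and do not restrict it.
- Section 7.1.3 defines an SAE without an underlying-disease exclusion, and Section 7.2.6 requires SAE reports whatever the cause. The life-threatening trigger is therefore not at issue.
- The Part 3 escalation review uses blinded safety data through Day 9, and liver tests are daily to that point, so the values need not arrive too late.

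The laboratory criteria in Section 7.2.2 also sit in a list of what an AE includes, so needing treatment is not a strict requirement.

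All of this stands and narrows the point. It does not remove it. The term toxicities is undefined, and the trigger counts them only when judged possibly or probably related. No section requires a causality judgement for a laboratory value that is not an AE. Section 10.4.2 specifies graded counts for Grades 3 and 4 only, without attribution, so moderate changes have no specified graded table.

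**Conclusion.** The point holds in a limited form. Section 7.2.2 contains two rules that give opposite answers for worsening hepatitis C, with no precedence. In Part 3, hepatic worsening short of clinical sequelae or an SAE can go unrecorded as an AE and unassessed for causality. The parts affected are the treatment-emergent AE component of the primary endpoint and the AE-based part of the suspension counts. The laboratory component, the Grade 3/4 tables, SAEs and any toxicities counted separately are not lost.

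The rule reaches all 70 to 80 planned subjects, but the number of events at stake is unknown because the protocol gives no rate. The probabilities above show only that, under assumed rates, recording half the events can cut the chance of reaching a count of two by roughly a half to two thirds (0.851 to 0.456 at p = 0.30; 0.264 to 0.086 at p = 0.10). They rest on hepatic worsening being the only qualifying event, on unrecorded events not being counted as toxicities or SAEs, and on the severity scale used. The disagreement among the laboratory-AE criteria is part of the same problem.

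**What to change.** 1. **Section 7.2.2.** For Part 3, limit the underlying-disease exclusion to chronic hepatitis C that is unchanged from baseline. Record on-study hepatic worsening as an AE and weigh hepatitis C in the causality field, as the possibly-related category in Section 7.2.3 already permits.
2. **Sections 7.1.2 and 7.2.2.** Replace the differing laboratory criteria with one rule based on worsening from baseline on a single named grading scale. At present Section 7.2.2 has its own scale, Section 7.2 points to DAIDS and Section 10.4.2 uses CTCAE v3.0.
3. **Section 5.1.1.** Name the severity scale. State whether toxicities include graded laboratory abnormalities and, if so, that these receive a causality assessment. The suspension thresholds are left to the sponsor.

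The cost is a wording amendment and matching CRF guidelines. There will be more AE entries and a somewhat higher reported AE rate in Part 3, placebo subjects included. Because entry ALT may be as high as 5 x ULN and Appendix E Grade 3 begins just above that, small drifts across a grade boundary may be recorded (for example 4.9 to 5.1 x ULN). The sponsor should consider this when writing the worsening-from-baseline rule.

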**7.2.3 Assigning Attribution of Adverse Events**

The investigator **must** attempt to determine the cause of each event. To ensure consistency of AE/SAE causality assessments, investigators should apply the following guideline:

**Related:**

There is an association between the event and the administration of investigational study drug, a plausible mechanism for the event to be related to the investigational study drug and causes other than the investigational study drug have been ruled out, and/or the event re-appeared on re-exposure to the investigational study drug.

**Possibly Related:**

There is an association between the event and the administration of the investigational study drug and there is a plausible mechanism for the event to be related to investigational study drug, but there may also be alternative etiology, such as characteristics of the subject's clinical status or underlying disease.

**Unlikely Related:**

The event is unlikely to be related to the investigational study drug and likely to be related to factors other than investigational study drug.

**Not Related:**

The event is related to an etiology other than the investigational study drug (the alternative etiology must be documented in the study subject's medical record).

**7.2.4 Classifying Action Taken with Study Drug**

| Classification   | Definition                                                                                                                                                                                                                                                                                                    |
|------------------|---------------------------------------------------------------------------------------------------------------------------------------------------------------------------------------------------------------------------------------------------------------------------------------------------------------|
| Dose Not Changed | Study Drug dose not changed in response to the AE                                                                                                                                                                                                                                                             |
| Dose Reduced     | Study drug dose reduced in response to an AE                                                                                                                                                                                                                                                                  |
| Drug Interrupted | Study drug administration interrupted in response to an AE                                                                                                                                                                                                                                                    |
| Drug Withdrawn   | Study drug administration permanently discontinued in response to an AE                                                                                                                                                                                                                                       |
| Not Applicable   | Action taken regarding study drug administration does not apply. "Not applicable" should be used in circumstances such as when the investigational treatment had been completed before the adverse event began and no opportunity to decide whether to continue, interrupt or withdraw treatment is possible. |

**7.2.5 Classifying Adverse Event Outcome**

| Classification                       | Definition                                                                                               |
|---------------------------------------------|-----------------------------------------------------------------------------------------------------------------|
| Recovered/Resolved                          | Resolution of an AE with no residual signs or symptoms                                                          |
| Recovered/Resolved with sequelae            | Resolution of an AE with residual signs or symptoms                                                             |
| Not Recovered/
Not resolved (continuing) | Either incomplete improvement or no improvement of an AE, such that it remains ongoing                          |
| Fatal                                       | Outcome of an AE is death. "Fatal" should be used when death is at least possibly related to the adverse event. |
| Unknown                                     | Outcome of an AE is not known (e.g., a subject lost to follow up)                                               |

**7.2.6 Documenting and Reporting Serious Pretreatment Events and Serious Adverse Events**

All SAEs that occur after obtaining informed consent through the Follow-up visit, regardless of causality, must be reported by the investigator to Icon Pharmacovigilance. In addition, all SAEs, including those that result in death, that occur after the Completion Visit and that are considered related to study drug(s) must be reported to Icon Pharmacovigilance within 24 hours.

SAEs will be recorded on the Clinical Trials SAE Form using a recognized medical term or diagnosis that accurately reflects the event. SAEs will be assessed by the investigator for severity, relationship to the investigational study drug(s) and possible etiologies. On the Clinical Trials SAE Form, relationship to study drug(s) will be assessed only as related or not related, and severity assessment will not be required. For the purposes of study analysis, if the event has not resolved at the end of the study reporting period, it will be documented as ongoing. For purposes of regulatory safety monitoring, the investigator is required to follow the event to resolution and report to Icon the outcome of the event using the SAE Form.

**The investigator is responsible for notifying the Sponsor within 24 hours of identifying an SAE, regardless of the presumed relationship to the investigational study drug. The SAE Form should be completed for new/initial events as well as to report follow-up information on previously reported events. Investigators are asked to report follow up information as soon as it becomes available, to ensure timely reporting to Health Authorities.**

